## Abstract

**Background:**

The combined application of long-lasting insecticidal nets (LLINs) and indoor residual spraying (IRS) are commonly used malaria interventions that target indoor Anopheles vectors. Recent studies on the effects of house screening (HS) and LLINs have demonstrated a reduction in indoor vector densities and malaria when the interventions are combined. In addition, complementary interventions are needed to curb co-occurring pest populations which pose menace to agricultural crop productivity and food security. However, interventions that impact malaria mainly centre on public health strategies, overlooking subtle but important component of agricultural measures. Addressing the coexisting risks of malaria and crop pests could contribute to improved livelihood of communities.

**Methods:**

A four-armed household, cluster-randomized, controlled study will be conducted to assess the combined impact of HS, LLINs and push-pull agricultural technology (PPT) against clinical malaria in children in Ethiopia. The unit of randomization will be the household, which includes a house and its occupants. A total of 838 households will be enrolled in this study. In this trial 246 households will receive LLINs and HS, 250 will receive LLINs, HS and PPT, 175 households will receive LLINs and PPT. The remaining 167 houses which receive LLINs only will be used as control. One child aged ≤14 years will be enrolled per household in each treatment and followed for clinical malaria using active case detection to estimate malaria incidence for two malaria transmission seasons.

**Discussion:**

Episodes of clinical malaria, density of indoor biting malaria vectors, sporozoite infection rate, improved crop infestation rate, crop yield gain, livestock productivity and cost effectiveness analysis will be the end points of this study. Socio-economic, social demographic, cost-effectiveness analysis will be conducted using qualitative and participatory methods to explore the acceptability of HS and PPT. Documenting the combined impact of LLINs, HS and PPT on the prevalence of clinical malaria and crop pest damage will be the first of its kind.

**Trial registration:**

Pan African Clinical Trials Registry, PACTR202006878245287. 24/06/2020. https://pactr.samrc.ac.za/TrialDisplay.aspx?TrialID=11101.

**Supplementary Information:**

The online version contains supplementary material available at 10.1186/s12889-022-12919-1.

## Background

Malaria continues to be a major health threat in Africa where 93 and 94% of the global cases and deaths, respectively, are reported [1]. Long-lasting insecticidal nets (LLINs), indoor residual spraying (IRS), rapid diagnostic tests (RDTs) and prompt disease treatment are key strategies being used in fighting the disease [2]. Despite the proven effectiveness of LLINs and IRS for malaria control, their effectiveness may be undermined by widespread occurrence of insecticide resistance in vector populations [3, 4]. Thus, we are interested to know the impact of house screening as a supplementary vector control tool, as search for innovative vector control expands to accelerate malaria elimination efforts [2].

House screening (HS), a promising supplementary vector control tool, is a valuable non-chemical strategy for preventing indoor biting by vectors, by acting as a physical barrier against entry into human dwellings [5–8]. HS could serve as a potential alternative to IRS, thereby reducing the dependence on chemical insecticides for malaria control. HS is also a cheaper alternative to IRS. Recent studies have demonstrated that house screening can significantly reduce the number of mosquitoes entering houses in The Gambia [9, 10], Tanzania [11] and Ethiopia [12, 13]. Despite this evidence, quantification of the large-scale impact of HS in different eco-epidemiological strata have been limited. A large-scale HS efficacy trial are being conducted across Africa in search of novel vector control intervention tools. These include the studies conducted in western [14, 15] and southern Africa [16]. The efficacy of any new intervention tool can be affected by several factors including malaria epidemiology, agro-ecology, and socio-cultural elements of the communities. Thus, any new tool should be evaluated against these parameters. In this study, we propose to conduct the evaluation of HS intervention in Ethiopia under different agro-ecology and malaria epidemiology settings. As part of the intervention, the doors, windows, and eves of the house will be screened with polyethylene material to assess the impact of HS intervention in northwest Ethiopia.

In addition to introducing HS for malaria vector control, we are interested to know the impact of providing farmers with agricultural technologies on productivity. This is because agriculture and health has always been interconnected in many ways. Increasing agricultural productivity improves the overall livelihoods of communities through improved health, nutrition, and income generation through sale of crops and livestock [17]. A study conducted in Uganda suggests that a 10% increase in overall household income would reduce malaria incidence by 35.6% [18]. In this trial, Push pull technology (PPT), a biological method used for maize pest control will be introduced to selected farmers to improve their maize productivity and improve animal feed. It is a novel technology in which a repellent intercrop and attractant trap plant is used simultaneously. The stem borers are repelled from the food crop and simultaneously attracted to a trap crop, which leads to minimal survival of the pests’ immature stages.

A combination of interventions is commonly evaluated to improve malaria outcomes. For instance, the joint implementation of LLINs and IRS were found to significantly reduce malaria incidence [19, 20], although no such effect was observed in other studies which assessed the combined effect of both [17, 21]. Few studies have evaluated the combined effect of LLINs and HS. We hypothesize that, HS can be considered as a preferable intervention to supplement with LLINs since its duration, cost and its effect on the environment is lower than IRS, which is entirely chemical based approach. Moreover, it can be applied in targeted areas where larval control could be impractical from agro-ecological perspective. The efficacy of screening doors, windows and eves on mosquito entry is well documented and it showed significant reduction in malaria vector mosquitoes [6, 9, 18, 22]. Study conducted in southern Ethiopia, indicated that screening materials fixed to doors, windows and eves lasted intact for at least 1 year which is double the age of longest IRS life span [23]. Thus, we propose to investigate the combined effect of LLINs and HS and LLINs, HS and PPT on entomological and epidemiological parameters.

The benefits of HS and PPT have been separately documented by several studies [8, 22–27]. Despite the evidence on the documented benefits, adoption of PPT and HS is quite limited. While PPT is adopted by only 260,000 farmers in sub-Saharan Africa [28], HS is still at the experimental stage [14, 29, 30]. The low adoption of these technologies necessitates not only introducing them in places where they are needed, but also evaluating their impact on health and livelihoods of the adopters of the technologies. How we best promote the technologies in the current study is also particularly interesting and will help draw lessons for the rest of Africa where the agricultural and health extension systems follow mostly a top-down approach of reaching farmers rather than being participatory [31].

### Trial objectives

#### General objective

The general objective of this intervention is to determine whether the combined intervention of long-lasting insecticidal nets, house screening and push-pull technology provide better protection against malaria and improves agricultural productivity in the intervention households compared to control households who received LLINs alone in Jabi Tehnan area, Northwest Ethiopia.

#### Specific objectives

i.To determine whether adding house screening of windows and doors of houses and implementing PPT reduces the rate of malaria parasite infection, parasite density, and anemia in children (aged between 5 to 14) compared to situations where only LLINs are used.ii.To assess whether the proposed interventions reduce human mosquito-interaction (human biting rates, mosquito resting density, longevity, sporozoite rates, and the entomological inoculation rate (EIR)) inside houses compared with LLINs alone.iii.To determine the incremental costs, benefits, and cost-effectiveness of adding house screening and PPT to usage of LLINs.iv.To assess the economic, social, and environmental feasibility of the combined intervention of house screening, LLINs and PPT.

## Methods

### Study setting and period

This study will take place between September 2020 and December 2022 in the Jabi-Tehnan district of Amhara regional state, Northwest Ethiopia. The capital town is Finote-Selam, which is about 387 km from the National capital, Addis Ababa, and 176 km Southwest of the regional capital, Bahir Dar. The population of the district was 211,516 in 2017 with an average annual growth rate of 2.8% [32]. The district is divided into 38 villages *(Kebeles),* which is the lowest administrative unit of the country, and three town administrations. More than 90% of the people in the district live in rural areas practicing mixed farming.

The altitude of the district ranges from 900 to 2300 m above sea level. Much of the area lies in the higher altitude range, closer to 2300 m. Agro-ecologically, 88% of the district is classified as mid land and the remaining 12% as low land. The topography of the district is dominated by areas of flat plain. According to Asmare & Gure, 2019 [33], the topography is classified as 65% flat plain, 15% mountainous, 15% undulating and 5% valley. The rainfall distribution is uni-modal, and the rainy season normally lasts for 4 months from mid-May to mid-September. The annual rainfall ranges 1250 mm per annum. The mean minimum and maximum temperatures are 14 °C and 32 °C, respectively [33]. According to the report compiled from 17 villages *(Kebeles)* of the district, malaria is a major health problem threat resulting in total mortality of 4345, and average Plasmodium annual parasite rate (API) of 11% ([name] 2018, personal communication). A cross sectional active malaria prevalence survey from randomly selected kebeles of the district in 2013 showed the disease prevalence of 2.8% [34]. According to the preliminary information collected from the district, houses are made of walls plastered with mud and roofs covered with corrugated iron sheet. According to the baseline survey conducted in the area 59% of the respondents reported that they keep the livestock in the same house but in separate rooms [35].

### Study participants

#### Population

The source population of this study will be the total population of the Jabi Tehnan district, Amhara Regional State, Northwest Ethiopia.

### Eligibility criteria

The study population will be all households that are found in the rural areas of Jabi-Tehnan district having at least one child (under 14 age) in their family.

### Sample size rationale

#### Sample size of houses for screening

Studies conducted in Ethiopia [12] and The Gambia [9, 10, 18, 36] have suggested that houses with their doors and windows screened can result in reduction of mosquito density measured between 40 to 70% as compared to control houses. In addition to mosquito proofing, house screening has proved to be effective intervention in reducing malaria incidence. Studies conducted to evaluate the impact of housing improvement on odds of malaria infection showed varying degree of efficacy. Tusting et al., [22], reviewed 53 published papers on housing and malaria interaction and reported 47% lower odds of malaria infection in ‘modern houses’ as compared to ‘traditional houses’. In Ethiopia, the protective efficacy of house screening was evaluated on 46 randomly selected households in Arba-Minch Zuria for 6 months and 61% reduction of malaria case was documented in screened houses as compared to the control houses [23]. In Kenya, malaria incidence was followed up in 80 screened houses for a year and 100% case reduction was reported [37]. Thus, considering the experiences from other countries and malaria prevalence information from the study area, this design is developed to measure the impact of house screening. A study conducted by Ayalew et al., (2016) [34] in 3 villages *(Kebeles)* in the district showed a 2.8% malaria prevalence and used as a benchmark for this trial. Accordingly, 838 households, will be selected from 30 villages *(Kebeles)*, using 80% power at the 5% significance level.

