**Fig. 1 Fig1:**
[figure not shown]
Flow chart of the study

In this study, a total of 167, 246, 250 and 175 houses will be included in four different treatments, treatment 1 (control, LLINs only), treatment 2 (LLINs and HS), treatment 3 (LLINs, HS and PPT) and treatment 4 (LLINs and PPT), respectively. The differences in sample size across arms is due to differences in number of households within each sub-village. To full fill the total sample size, we did the random selection based on population size of each sub-village. Census of children under 14, and above 14 years of age will be made in all 838 households selected. One child will be randomly selected from each house for annual malaria parasite survey. In addition to the annual parasite screening survey, monthly follow up will be implemented in all households to monitor clinical malaria by health extension workers. If a child moves or quits the study, we will replace the child from the same house. In instances where the whole family leaves the area, we will document them as lost to follow up.

The selected children will be checked up every month for clinical symptoms of malaria infection, splenomegaly, and development of anaemia. Blood test will be conducted if the child develops clinical symptoms. The child will also be surveyed at the beginning and end of each transmission season to estimate the prevalence of *Plasmodium species* infection, parasite density, and the prevalence of anaemia. Collections will be made from both indoor and outdoor settings.

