### Statistical methods

#### Malaria incidence data analysis

Change in clinical malaria incidence over 2 years period among the treatment and control arms will be determined using Poisson distribution. In this trial we will follow modified ITT protocol and if a child is lost from follow up, or withdraw from the study, or refuse to be included in the treatment, it will be immediately replaced by a child from the reserve list. The Relative Risk (RR) and RR Reductions (RRR) will be calculated with corresponding 95% confidence intervals to compare dichotomous variables, and difference in means will be used for additional analysis of continuous variables. Mixed effects Poisson model will be used to test the difference in incidence rates among the study arms, to determine effects of the repeated measurements within house, village, the effect of year and village-intervention interaction effects. To control the effect of clustering or village and individual level confounding factors such as gender and age, these covariates will be fitted in to random effects during analysis. If a child is diagnosed with malaria case within 28 days of the first episode with the same plasmodium species, then it will be put on treatment as part of the safety protocol, however, the case will not be included in the analysis. The prevalence of anaemia among the study participants (children) will be analysed using the guideline developed by world health organization [47]. Accordingly, all children between 6 and 59 months of age, whose Hb level is recorded between 10.0–10.9 g/dl, 8.0–9.9 g/dl and less than 8.0 g/dl will be graded as mild, moderate, and severe, respectively. In line with this we will also report community level anaemia prevalence. Thus, a prevalence of anaemia will be stated as severe if it is documented over 40% (combining mild, moderate, and severe) and moderate if the prevalence is 20–39.9%. Both malaria and anaemia prevalence data will be compared in the intervention and control houses using multilevel mixed-effects logistic regression models, taking village effects into account.

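### The protocol's inputs do not support 80% power for 838 households: at the 2.8% benchmark, the cited 47% and 61% malaria reductions give far less

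*Protocol article*

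**What the plan says.** The section on the sample size of houses for screening lists earlier results: 40 to 70% fewer mosquitoes, 47% lower odds of malaria infection in a review of housing studies, "61% reduction of malaria case was documented in screened houses as compared to the control houses" in an Ethiopian study, and a 100% case reduction in Kenya. It then says that a survey in the district "showed a 2.8% malaria prevalence and used as a benchmark for this trial", and concludes: "Accordingly, 838 households, will be selected from 30 villages", "using 80% power at the 5% significance level". It does not say which reduction, comparison, sidedness or clustering allowance lies behind 838.

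Three other places bear on this figure:
- The text under the flow chart fixes the arms: "a total of 167, 246, 250 and 175 houses will be included in four different treatments", in the order control, LLINs + HS, LLINs + HS + PPT, LLINs + PPT.
- The malaria incidence analysis section takes as its outcome "Change in clinical malaria incidence over 2 years period among the treatment and control arms", analysed with a Poisson model.
- The sequence generation and randomization sections allocate 66 sub-kebeles to the four arms.

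The study setting section gives a second local rate, "average Plasmodium annual parasite rate (API) of 11" per cent.

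**The concern.** The text presents 838 households as the consequence of the 2.8% benchmark at 80% power. With 167 control children, 2.8% is 167 × 0.028 = 4.7 expected positives, which is very little to detect a partial reduction against. A null malaria result would be read as coming from a trial with 80% power, and the Conclusion section says the findings will inform national malaria programmes.

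The benchmark also measures something different from the outcome. It is a one-survey prevalence, while the analysis counts clinical episodes over two years. Whether the trial is adequately powered depends on the yearly rate, which the sample size section does not give.

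**Working it through.** **Inputs from the protocol article.** Control proportion 0.028; arms 167, 246, 250 and 175; screened 246 + 250 = 496; unscreened 167 + 175 = 342; cited malaria reductions 47% (stated as odds), 61% and 100%; 66 sub-kebeles, mean 838/66 = 12.7 households. The 40 to 70% range is mosquito density, not malaria, and is left out.

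**Assumptions made here.** Two-sided 5%; 2.8% and 11% as yearly rates; between-cluster coefficient of variation (CV) from 0 to 0.5.

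**1. Trying to reproduce 838.** No effect size is stated, so each cited one was tried with the pooled-variance two-proportion formula, equal arms and 80% power:

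| Reduction | Per arm | Two arms | Four arms |
|---|---|---|---|
| 47% | 1,899 | 3,798 | 7,596 |
| 61% | 1,026 | 2,052 | 4,104 |
| 100% | 276 | 552 | 1,104 |

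None gives 838, nor do the one-sided or continuity-corrected variants. Split 419 + 419, 838 households reach 80% at a reduction of about 86.5%.

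**2. Power on the prevalence reading, no clustering.** Power = Φ[(p1 − p2 − 1.96·s0)/s1], where s0 is the standard error under the pooled proportion and s1 the unpooled one.

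Arm 2 against control, 61%: p2 = 0.028 × 0.39 = 0.01092, s0 = 0.01327, s1 = 0.01438. Power = Φ[(0.01708 − 0.02600)/0.01438] = Φ(−0.62) = 27%.

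| Comparison | 47% | 61% | 100% |
|---|---|---|---|
| Arm 2 v control (246 v 167) | 17% | 27% | 71% |
| Arms 2+3 v control (496 v 167) | 23% | 37% | 85% |
| Screened v unscreened (496 v 342) | 28% | 45% | 93% |

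Taking 47% strictly as an odds reduction gives 16% and 27% in the first and last rows.

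**3. Power for a two-year rate ratio.** Power = Φ[−ln(1 − r)/SE − 1.96], where r is the reduction and SE = √(D1/E1 + D2/E2). E is expected episodes over two years, and D = 1 + CV² × 12.7 × (that arm's yearly rate) × 2.

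Arm 2 against control at 2.8% per year, 61%, CV 0: E1 = 167 × 2 × 0.028 = 9.35; E2 = 246 × 2 × 0.028 × 0.39 = 5.37; SE = 0.541. Power = Φ(0.942/0.541 − 1.96) = Φ(−0.22) = 41%.

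| Yearly control rate | Comparison | CV | 47% | 61% |
|---|---|---|---|---|
| 2.8% | Arm 2 v control | 0 | 25% | 41% |
| 2.8% | Arm 2 v control | 0.5 | 23% | 38% |
| 2.8% | Screened v unscreened | 0 | 45% | 70% |
| 2.8% | Screened v unscreened | 0.5 | 41% | 65% |
| 11% | Arm 2 v control | 0 | 72% | 93% |
| 11% | Arm 2 v control | 0.5 | 54% | 82% |

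A different two-sample Poisson formula gives 44% and 71% where the 61% column shows 41% and 70%.

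**The case against.** A reader might infer that 838 households could not reach 80% at 2.8% even if screening eliminated malaria, so that the figure is plainly wrong. The documents do not support that. Elimination gives 71% for arm 2 against control by the usual formula (69% by Fisher's exact test). It gives 85% for control against arms 2 and 3, 93% for screened against unscreened, and 85% for arm 2 against control with an uncorrected chi-square test. The sample size section names no contrast, only the impact of house screening, and it does cite one study with a 100% reduction. On the outcome actually analysed, an 11% yearly rate with a 61% reduction gives 93%, or 82% with clustering at CV 0.5.

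Sidedness is also unstated. One-sided, the most favourable 2.8% reading (yearly rate, pooled, 61%) gives Φ(0.942/0.380 − 1.645) = 80% before clustering. It drops to 76% at CV 0.5.

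A condensed article may leave the intracluster correlation to the full protocol, so its absence alone is no fault. The CVs used here are assumptions.

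Finally, comparing each arm with control is legitimate, since the general objective sets the combined package against LLINs alone. That the four arms form a 2×2 of HS by PPT does not make this an error, and the Discussion hypothesises synergy, which a pooled contrast would average over.

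What stands against all this is that the article does state a result and the inputs from which it is said to follow, and those inputs do not lead to it.

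**Conclusion.** The concern holds in this form: the 80% statement is not supported by the inputs given. At 2.8% and two-sided 5%, neither cited malaria reduction short of elimination reaches 80% in any comparison tried. Power runs from 17% (arm 2 against control, prevalence, 47%) to about 70% (pooled, 2.8% assumed per year, 61%), all before clustering. Reaching 80% on the prevalence reading needs a reduction of about 86%, even with all 838 households in one two-group comparison.

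The true power is not known to be low. It could be adequate if the yearly rate is nearer 11%, and the article does not say which rate, reduction or comparison was meant. Randomising sub-kebeles lowers every figure further if risk varies between them; by how much depends on a CV that the article does not give.

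**What to change.** Withdraw the unqualified 80% statement. Restate power for the incidence rate ratio, giving:
- the named comparison and the actual arm sizes;
- the assumed control rate, showing both 2.8% and 11% as assumed yearly rates;
- the assumed reduction and the sidedness of the test;
- a clustering allowance for the 66 sub-kebeles, shown as a range.

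Do not enrol more households on this account. The cost is a rewritten paragraph and, under some assumptions, a less favourable figure.

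Optionally, add the HS contrast stratified by PPT (arms 2+3 against 1+4) as a supporting analysis, not as a replacement for the comparisons with control. Its variance is smaller by (1/167 + 1/246)/(1/342 + 1/496) = 2.03. At an assumed 11% per year, a 47% reduction and CV 0.5, power would be 84% rather than 54%. It assumes little HS-by-PPT interaction on malaria, so report the HS-by-PPT ratio with its interval beside it and state that caveat. The cost is one extra contrast in the same Poisson model.
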